### Statistical analysis

The full statistical analysis will be written into a statistical analysis plan available separately. The analysis will produce a Consolidated Standards of Reporting Trials diagram for the reporting of clinical trials.

The baseline characteristics of the two groups will be tabulated but not tested for statistically significant differences between the groups.

The primary analysis is by intention to treat. However, an investigation of compliance with the treatment pathway and compliance with the criteria for changing to a second-line therapy will be carried out prior to the primary analysis to check the date of the primary event. The primary event is the date at which there was a requirement for second-line therapy. Where the platelet count falls below the level required for this treatment decision, the first date at which either symptoms or a blood test revealing this event will be used. If a clinician decides to use a second-line therapy without a platelet count below the criteria, the date of the treatment decision/new prescription will be taken to represent that event. The results will be expressed as an HR with 95% CI, median time to event if more than 50% have had an event and plotted as Kaplan-Meier curves.

The primary analysis will contain all patients who are randomised for as long as they have been followed up or until their first event in a survival analysis using intention to treat methodology. All patients will be followed up to 12 months. In addition, patients who have not had an event in the first 12 months postrandomisation will be followed until their first event or until the last patient has reached the 12-month point—whichever is the sooner and included in the analysis until that time accordingly. Sensitivity analyses will include landmark analysis or shifting the time line to classify all treatment failures before 2 months as at 2 months in order to prevent potential biases caused by different definitions of treatment failure time frames between the two groups.

Analysis of other outcomes will use as full a data set as possible and focus on the 12-month data point or area under the curve as appropriate and detailed in the analysis plan.

No interim analyses of the main endpoint will be supplied to the independent data monitoring committee (DMC) due to the short time frame (12 months recruitment) in which all patients will be recruited by the time the first patient has completed follow-up. Serious adverse event (SAE) rates will be reported on a monthly basis to the TMG and the DMC. The DMC could advise the chairman of the trial steering committee and chief investigator if these provide proof beyond reasonable doubt that it would be unethical to continue with the trial.

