**Primary outcome:**

Time from randomisation to treatment failure defined as platelets <30x10^9^/L and a need for second-line treatment.

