Current first-line ITP treatment is with high-dose corticosteroids but this has several downsides. First, the majority of patients suffer significant side effects including mood swings, difficulty sleeping, weight gain, high blood pressure, diabetes, gastric irritation, skin thinning and osteoporosis. A published survey of patients with ITP reported 98% had at least one side effect and 38% stopped or reduced dosage due to intolerable side effects.^8^ In the UK ITP registry, the most frequently reported comorbidities were related to corticosteroids and correlated with duration of treatment (hypertension in 30%, diabetes in 19%).^9^ The second problem is that patients are heterogeneous in their response to corticosteroid with some (approximately 20%) not responding at all and the majority of others (70%–90%) relapsing when the corticosteroids are reduced or stopped.^7 10 11^Patients, who are refractory or relapse (the majority), remain at risk of bleeding/bruising, which occasionally can be severe including intracranial haemorrhage.^12^ They often receive more corticosteroid with associated side effects. Some require hospital admission and expensive rescue therapies (eg, intravenous immunoglobulin, Ig for a 70 kg patient=£3906). They continue to require frequent blood tests and doctor visits and are usually unable to continue their normal activities until their illness is controlled. Fatigue is also associated with disease activity and can be severe.^13^ Physical factors combine with psychological stress through fear of bleeding, need for time off work and lifestyle restrictions due to bleeding risk to adversely impact quality of life.^14 15^

First-line treatment for ITP is unsatisfactory but it remains unchanged for decades. Although a small number of studies have tested alternative approaches, a well-tolerated, effective and durable new approach has not been conclusively demonstrated. High-dose corticosteroid remains the standard first-line treatment recommended in most countries.^10^

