### Primary outcome

Time from randomisation to treatment failure defined as a platelet count <30×10^9^/L and a need to commence second-line treatment. This will include patients who are refractory (platelet count <30×10^9^/L in spite of 2 weeks treatment in the steroid arm or platelet count <30×10^9^/L in spite of 2 months treatment in the steroid +MMF arm) or who initially respond but then relapse (defined clinically as platelet count <30×10^9^/L and need for further therapy). Patients with a clinical need to start second-line treatment early (within 2 weeks for the steroid only arm and within 2 months for the MMF and steroid arm), for example, due to significant bleeding, will also be classed as treatment failures.

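### The endpoint definition and the analysis rule state two different primary events: one requires a platelet count below 30×10^9/L, the other counts a second-line start without it

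*Protocol article*

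**What the plan says.** The Primary outcome section of the protocol article gives a two-part definition: "Time from randomisation to treatment failure defined as a platelet count <30×10^9^/L and a need to commence second-line treatment". The abstract has the same conjunction: "Time from randomisation to treatment failure defined as platelets <30x10^9^/L and a need for second-line treatment". Both regular routes to failure in the Primary outcome section, refractory disease and relapse, repeat the platelet condition.

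That section allows one exception. Patients with a clinical need to start second-line treatment early (within 2 weeks in the steroid arm, within 2 months in the MMF arm), "for example, due to significant bleeding, will also be classed as treatment failures". No platelet level is named for them.

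The Statistical analysis section works differently. It opens with "The primary event is the date at which there was a requirement for second-line therapy", which has no platelet condition. It then continues: "If a clinician decides to use a second-line therapy without a platelet count below the criteria", the date of that decision or prescription represents the event. It sets no time limit and asks for no reason.

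The same section plans a review of compliance with the pathway and with the switching criteria, but gives its purpose only as checking the event date. Its sensitivity analyses are a landmark analysis or moving all failures before 2 months to 2 months. The Secondary outcomes section lists time to next therapy as a separate outcome.

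**The concern.** The two rules differ on who has an event, not only on when. A patient who starts a second-line drug at month 5 with a count of 80×10^9/L is a primary failure under the Statistical analysis section and is not one under the Primary outcome section.

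The trial is open label and the choice of second-line drug is individualised, so under the broader rule an unblinded treatment decision is enough to create a primary event. The Introduction describes MMF as a widely used second-line drug in the UK, and it is still unused in the steroid arm. If more patients with adequate counts are switched in one arm than in the other, the hazard ratio partly measures tolerability and clinician preference instead of the stable platelet count named in the Primary objective. The broader rule also brings the primary outcome close to time to next therapy, which the protocol lists separately.

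**Working it through.** **1. Do the rules conflict?**

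| Second-line start | Primary outcome section | Statistical analysis section |
|---|---|---|
| Count below 30, treatment needed | event | event |
| Count 30 or more, early window, clinical need | event | event |
| Count 30 or more, early window, no such need | not an event | event |
| Count 30 or more, after the early window | not an event | event |

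The conflict lies in the last two rows.

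**2. Reproduce the stated power.** Inputs from Sample size calculation: 60 per arm, medians 5 and 10 months, 12 months of accrual, analysis at month 24. Assumed: exponential times and two-sided 5% (the article does not state alpha).

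- Hazards: ln2/5 = 0.1386 and ln2/10 = 0.0693 per month.
- P(event) = 1 − (e^(−12λ) − e^(−24λ))/(12λ), which is 0.908 and 0.704.
- Expected events: 54.5 + 42.3 = 96.7 (from unrounded values).
- Power = Φ(√96.7 × ln2/2 − 1.96) = Φ(1.45) = 92.6%. With 57 per arm (5% lost) there are 91.9 events and 91.3% power.

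The stated 91.5% is reproduced and is not in dispute.

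**3. Effect of above-threshold starts when MMF has no effect on platelet failure** (median 5 months in both arms). The article gives no rate of such starts, so every rate here is an assumption.

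*Constant extra hazard.* A 12-month risk r, in the absence of platelet failure, gives d = −ln(1−r)/12. The expected hazard ratio is (0.1386 + d_MMF)/(0.1386 + d_steroid). False-positive rates are from 8,000 simulated log-rank trials per row.

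| Steroid arm | MMF arm | HR | False positive favouring MMF |
|---|---|---|---|
| 5% | 0 | 0.97 | 3.5% |
| 10% | 0 | 0.94 | 5.2% |
| 20% | 0 | 0.88 | 10.1% |
| 20% | 10% | 0.94 | 5.2% |
| 10% | 10% | 1.00 | 2.6% |
| 0 | 10% | 1.06 | 1.2% |

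Example: r = 10% gives d = 0.00878, and 0.1386/0.1474 = 0.94.

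*Fixed fraction of the steroid arm assigned a switch date, none in the MMF arm* (4,000 simulated trials per row; a switch counts only if it comes before platelet failure).

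| Fraction | Timing | HR | False positive favouring MMF |
|---|---|---|---|
| 10% | spread over 12 months | 0.95 | about 5% |
| 10% | weeks 2–10 | 0.91 | about 7% |
| 19% | spread over 12 months | 0.90 | about 7–8% |
| 19% | weeks 2–10 | 0.83 | about 16% |

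Timing alone roughly doubles the false-positive rate at 19%.

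**4. Effect when the true HR is 0.5** (constant-hazard model).

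- 10% in both arms: (0.0693 + 0.0088)/(0.1386 + 0.0088) = 0.53, power about 89%.
- 10% in the MMF arm only: (0.0693 + 0.0088)/0.1386 = 0.56, power about 82%.
- 20% in the steroid arm only: 0.0693/(0.1386 + 0.0186) = 0.44, power about 98%.

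**5. Do the listed safeguards cover it?** The compliance review, as described, checks dates. The 2-month shift removes no events. A landmark removes those before the landmark: with one assumed at 2 months, the scenario of 19% at weeks 2–10 goes from HR 0.83 and 16% to about 0.96 and 4%, because about 84% of those switch dates fall before 2 months. It leaves later starts untouched.

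**6. Cost of the strict rule.** With a true HR of 0.5, suppose 19% of controls switch at weeks 2–10 and then have the MMF-arm hazard. Not scoring the switch and following to platelet failure gives an HR of about 0.55, and power falls from about 92% to about 79%.

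**The case against.** A reader might infer that the rule creates events that favour MMF. The documents do not support that as a fact. They give no rate of above-threshold starts in either arm. Both arms follow the same steroid taper, and the section headed In both groups allows steroid dose and duration to vary for tolerability, so a steroid-arm responder with side effects can have steroid reduced without a new drug. MMF intolerance followed by another second-line drug would count against MMF. The direction is plausible, no more.

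A reader might also size the problem from the Introduction's survey figure, "38% stopped or reduced dosage due to intolerable side effects". That figure describes stopping or reducing steroid, not starting second-line treatment at an adequate count, so no fraction of it serves as a switch rate.

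A third tempting reading is that no planned analysis touches these events. The landmark option does, for early starts. But the protocol offers it as an alternative to the time shift, names no landmark month, and does not make it primary.

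Finally, counting a second-line start as failure is a legitimate endpoint, and the strict rule has a real cost in power. The strict rule also keeps early-need windows of unequal length, which admit events without a low count for 2 months in the MMF arm but only 2 weeks in the steroid arm. This argues against presuming which definition should be primary. It does not remove the need to state one. Nor can the matter be left to the statistical analysis plan as missing detail, because the article states both rules and they disagree.

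**Conclusion.** The concern holds as an inconsistency in the primary endpoint. It is clear for second-line starts after the early windows and for early starts without clinical need; it does not arise for early starts with clinical need. Under open-label treatment it leaves the hazard ratio open to bias from discretionary switching.

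The size is conditional. With no true effect and 10–20% above-threshold starts in the steroid arm only, the hazard ratio is about 0.95 to 0.83 and the false-positive rate favouring MMF about 5% to 16%, against 2.5%. The upper end needs switching that is early and confined to the steroid arm. Equal switching gives no false positives and dilutes a true effect; excess switching in the MMF arm biases against MMF. All of this assumes exponential times and rates that the documents do not supply. Severity: should be fixed before analysis.

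**What to change.** 1. Make the abstract, the Primary outcome section and the Statistical analysis section state the same primary event, and settle it before the data are analysed.
2. Run the other definition as a named sensitivity analysis, so that the two results can be read side by side.
3. In the strict analysis, do not censor patients who start second-line treatment above the threshold, because that censoring would be informative. Follow them to the first qualifying low count. State that second-line benefit in switched controls makes this analysis conservative and costs power (about 92% to 79% in the scenario above).
4. Extend the planned compliance review so that above-threshold starts are reviewed blind to arm, and report their number and reasons by arm.

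The cost is a paragraph of text, one further model and a short table. Platelet counts and treatments are already collected in all patients to at least 12 months, so no new visits are needed.

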### Pharmacovigilance

The collection and reporting of all adverse events is in accordance with the Medicines for Human Use Clinical Trials Regulations 2004 and its subsequent amendments and follows the standard operating procedures of the trials unit, Cardiff University CTR.

Seriousness and causality are assessed by participating sites and further review of expectedness (based on the reference safety information) is conducted centrally on behalf of the Sponsor. Events are defined as SAEs, serious adverse reactions (SARs) or suspected unexpected SAR in line with regulatory definitions on the basis of these assessments.

SAEs are reported throughout the treatment period up to 6 weeks after cessation of last dose of MMF. SARs should continue to be reported until the end of follow-up. All deaths and overdoses are reported to the sponsor as an SAE and reviewed in line with other events.

MMF in this trial has a genotoxic and teratogenic potential and therefore pregnancy is contraindicated. Participants who are female of childbearing potential or male with female partners of equal potential are required to use contraception as indicated in the protocol. Pregnancy or the pregnancy of a partner occurring while participating in the trial is not considered an SAE, however, a congenital anomaly or birth defect is. Pregnancy is reported to sponsor and followed up to outcome.

All safety events are reviewed by the TMG on an ongoing basis and reported to the trial steering committee for oversight. Overall assessment of the safety profile of both arms will be included in final reporting and publication.
